### **Power**

The proposed study builds on a descriptive study that provides baseline data for all proposed sites. This allows us to use parameter estimates from the sample under study to estimate the power of the proposed study to detect effects. Analyses have been conducted using data from each study community collected in 2000. Thus, our power analyses provide very accurate assessments of the differences between intervention and control groups that can be observed with adequate power.

The power analyses for adolescent outcomes assume that children are nested within communities. A three level structure in which students are nested within schools nested within communities is also possible. Separate three level power analyses were conducted and only small differences were found for the more complex design. Further, all analyses assumed continuously varying, normally distributed outcomes. While this assumption is violated for binary outcomes, simulations have found that, given at least 30 members per group, the Central Limit Theorem still holds and the analyses will still provide adequate parameter estimates (Hannan & Murray, 1996).

Power was estimated for analyses using a simple comparison of the experimental and control groups, then for analyses using a matched pair design, and finally for analyses using matched pairs in which

1998 average community levels of each outcome is included as a community-level baseline covariate. While the longitudinal data we have for the communities does not yet extend for more than two years, including the 1998 scores allows an assessment of the ability to detect how the intervention is related to change in communities rather than just differences in community means. The principal task in power analyses is to find an estimate of the variance of the treatment effect,  $\sigma\Delta$ . Then t-statistics can be calculated and formulas can be applied to find the power for any given treatment effect. As described in Appendix G, the power of the proposed study was calculated by first finding the standard error of the treatment effects (Bryk & Raudenbush, 1992; Murray, 1998; Raudenbush, 1997; Raudenbush et al., 2000) and then using these standard errors to find the detectable treatment effect with a power of .80.

Estimates of  $\sigma\Delta$  were found by using data from the study communities. Since the community is the level of random assignment, the sample size is 24 (Murray, 1998). Analyses were done using only eighth grade students since that is the grade expected to be most directly affected by the intervention. For the sake of brevity, two representative risk factors and the most relevant behavioral outcomes for the targeted age group were used in the power analyses.

We found that in most cases use of the matched pairs design reduced the community-level variance enough to result in an increase in power even when taking into account the loss of degrees of freedom. Further, the addition of 1998 baseline outcome measures as community-level covariates generally resulted in large decreases in community-level variance resulting in further increases in power. The power of the matched pairs analyses with community-level covariates is reported in Table 3. For a full description of these analyses, see Appendix G.

Results of these analyses indicate that this study has adequate power to detect differences in student's risk and protective factors equivalent to a small effect size of .25. Effect sizes of .2 or larger are generally considered to be small but of practical significance, while effect sizes of .50 and above are generally considered large in social science research (Cohen, 1977). The study has power to detect differences of 12% in rates of lifetime use of alcohol, 7% in rates of lifetime use of cigarettes, and 7% in rates of alcohol use during the past month (a 22, 16, and 25% reduction, respectively). Average prevalence rates for these variables are reported in Table 3 in the means column. These effects are at the low end of the range of what has been demonstrated by other successful community-level interventions which have found reductions in initiation of alcohol and cigarette use in the eighth grade of between 20 and 40% (Pentz et al., 1997; Perry et al., 2000; Perry et al., 1996). The detectable difference for risk factors is based on the 4-point scale measuring these constructs.

The power reported here for the child level outcomes is expected to be the minimum that is observed in the longitudinal analyses both at the community level and at the child level in the longitudinal panel.

Secondly, an examination of the power of the study to detect changes in implementation scores from three or less to above three was conducted using non-parametric techniques. These analyses found the study will have adequate power to detect a significant difference if six more experimental communities than controls achieve the desired implementation result.

**Table 3: Detectable Differences in Eighth Grade Student Outcomes  
Between Intervention and Control Groups**

| Outcome                              | M (SD) | Power
0.80 | Effect Size/
% Reduction* |
|--------------------------------------|---------------|-----------------------------|--------------------------------------------|
| Total Risk Score                     | -0.02 (.58)   | 0.120                       | .21                                        |
| Total Protection Score               | -0.05 (.63)   | 0.184                       | .28                                        |
| Favorable Attitudes Towards Drug Use | 1.60 (.75)    | 0.184                       | .25                                        |
| Perceived Risk of Drug Use           | 1.85 (.76)    | 0.131                       | .18                                        |
| Friends' Use of Drugs                | 0.90 (1.06)   | 0.262                       | .25                                        |
| Lifetime Cigarette Use               | 0.43          | 0.078                       | 18%                                        |
| Lifetime Alcohol Use                 | 0.52          | 0.130                       | 25%                                        |
| 30 Day Alcohol Use                   | 0.27          | 0.078                       | 29%                                        |
| Violence                             | 0.15          | 0.058                       | 37%                                        |
| Delinquency                          | 0.22          | 0.075                       | 35%                                        |

\*  $\beta = 0.80$

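### The Power text and Table 3 disagree on the detectable differences for three substance-use outcomes; if Table 3 is right, power at the text's figures is about 71 to 74%, not 80%

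*Protocol*

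**What the plan says.** The Power section (Protocol) describes one route to its figures. Standard errors of the treatment effect were estimated from the study communities' own 2000 data, and the detectable effects were obtained by "using these standard errors to find the detectable treatment effect with a power of .80". The unit count is fixed by the randomisation: "Since the community is the level of random assignment, the sample size is 24". Three designs were considered, and the tabulated one is named: "The power of the matched pairs analyses with community-level covariates is reported in Table 3".

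The narrative then gives these results:
- For risk and protective factors, "adequate power to detect differences in student's risk and protective factors equivalent to a small effect size of .25".
- For behaviour, "The study has power to detect differences of 12% in rates of lifetime use of alcohol, 7% in rates of lifetime use of cigarettes". The figure for 30-day alcohol use is 7 points. The relative reductions for lifetime alcohol, lifetime cigarettes and 30-day alcohol are put at 22%, 16% and 25%. The reader is referred to the means column of Table 3 for the underlying prevalences.
- On context, "These effects are at the low end of the range of what has been demonstrated by other successful community-level interventions", where the cited range is a 20 to 40% reduction in initiation of alcohol and cigarette use by eighth grade.

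"Table 3: Detectable Differences in Eighth Grade Student Outcomes" has a column headed Power 0.80. It gives 0.130 (25%) for lifetime alcohol, 0.078 (18%) for lifetime cigarettes and 0.078 (29%) for 30-day alcohol. For the scales, the effect sizes are .21 (Total Risk), .28 (Total Protection), .25, .18 and .25.

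**The concern.** The text and the table are presented as the same calculation: same eighth-grade data, same matched-pairs design with baseline covariate, same power. They should therefore show the same numbers, and for the three outcomes named in the text they do not. The text offers no second power level, significance level or design that would explain the difference.

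These sentences are the protocol's headline statement of what the trial can detect. The section also says that this power is the minimum to be expected in the longitudinal analyses. Someone who later reads 12, 7 and 7 points as the 80%-power limits would credit a null result with excluding effects for which the design, on Table 3's figures, falls short of 80% power.

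**Working it through.** **Inputs.** Table 3 means: 0.52 (lifetime alcohol), 0.43 (lifetime cigarettes), 0.27 (30-day alcohol). Table 3 detectable differences at power 0.80: 0.130, 0.078, 0.078. Text differences: 0.12, 0.07, 0.07. The protocol states no significance level; two-sided 0.05 is assumed and varied below.

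**1. Does Table 3 agree with itself for these rows?** Relative reduction = difference / mean.
- Lifetime alcohol: 0.130/0.52 = 25.0% (printed 25%)
- Lifetime cigarettes: 0.078/0.43 = 18.1% (printed 18%)
- 30-day alcohol: 0.078/0.27 = 28.9% (printed 29%)

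It does.

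**2. Can the text be a rounding of Table 3?** No. 13.0 neither rounds nor truncates to 12. 7.8 rounds to 8; truncation would give 7, but would leave the alcohol figure and the 22, 16 and 25% unexplained. From the table means, the text's whole-point differences give 0.12/0.52 = 23.1%, 0.07/0.43 = 16.3% and 0.07/0.27 = 25.9%. The printed 22, 16 and 25% are therefore close to the text's own differences and clearly away from the table's percentages.

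**3. Power at the text's differences if Table 3 is correct.** The table's difference D has 80% power, which fixes the standard error. In the normal approximation SE = D/(1.960 + 0.842) = D/2.802, so power at difference d is Φ(2.802 × d/D − 1.960).
- Lifetime alcohol: Φ(2.802 × 0.12/0.13 − 1.960) = Φ(0.626) = 73.4%
- Lifetime cigarettes and 30-day alcohol: Φ(2.802 × 0.07/0.078 − 1.960) = Φ(0.554) = 71.0%

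The noncentral t with 10 degrees of freedom (12 pairs, one covariate) has noncentrality 3.11 at 80% power and gives 73.5%, 71.1% and 71.1%. Using 9, 11 or 22 degrees of freedom changes nothing beyond the third decimal. With one-sided 0.05 the values are 74%, 72% and 72%.

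**4. Sensitivity to how the text was rounded.**
- If 12 and 7 stand for values just under 12.5 and 7.5 points, power is at most about 77%.
- If the text's percentages are used instead, the differences are 0.22 × 52 = 11.4, 0.16 × 43 = 6.9 and 0.25 × 27 = 6.75 points, and power is about 69%, 70% and 68%.

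**5. The .25 summary for risk and protective factors.** Total Protection is printed as .28, and its own entries give 0.184/0.63 = .29. Power at .25:
- with .28: Φ(2.802 × .25/.28 − 1.960) = Φ(0.542) = 71%
- with .292: Φ(2.802 × .25/.292 − 1.960) = Φ(0.439) = 67%

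The other four scales are at or below .25.

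**The case against.** The strongest reply is that nothing in the protocol body shows which set of figures is current. The derivation is in Appendix G, which is not reproduced. If the narrative came from a later run, Table 3 is the stale version and there is no power shortfall. This stands. A reader might infer that the study simply has 71 to 74% power for its stated effects; the documents support that only on the condition that Table 3 is right.

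Other tempting readings go further than the documents allow:
- **That the text ignored the few community-level degrees of freedom.** The text figures are about 0.90 times the table's, which is close to the ratio of the normal multiplier to the t multiplier on 10 degrees of freedom. But Table 3 rescaled to 70% power (noncentral t, 10 degrees of freedom) gives 11.5, 6.9 and 6.9 points, which fits about as well. The section also speaks of t-statistics and of allowing for lost degrees of freedom. The cause cannot be identified.
- **That the comparison with earlier trials must be withdrawn.** On Table 3's figures, 18% for cigarettes is below the 20 to 40% range and 25% for lifetime alcohol is in its lowest quarter. Thirty-day alcohol, at 29%, is current use rather than initiation, so the range does not directly apply to it.
- **That incomplete exposure raises the required effects further.** The two-thirds exposure assumption for larger communities serves the participant counts in Table 4. The Intervention section describes work on norms, policies and media across the whole community, so treating unexposed youths as unaffected is not supported.

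It is also fair to say that the gap is only 0.8 to 1.0 percentage points, that the 80%-power values are printed in the table, and that the communities are already recruited and randomised. That limits the severity but does not remove the contradiction. On the .25 summary, one number for five scales is a simplification, and the exception is openly printed.

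**Conclusion.** The contradiction is real. For three outcomes the text and Table 3 give different detectable differences for what is presented as one analysis, and all six text figures are the more favourable ones. Conditional on Table 3 being correct and on a two-sided 0.05 test, power at the text's differences is about 71 to 74%, with a ceiling of about 77% for rounding. The agreement of these three rows with their own means, and the text's naming of the table as the report of results, make Table 3 the more likely version but do not prove it. The .25 summary does not cover Total Protection, where power at .25 is about 67 to 71%. Severity is moderate: no sample size, design or analysis depends on these sentences, but they misstate the detectable effects unless the table is the part in error.

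**What to change.** Check the narrative and Table 3 against Appendix G, and make them agree. State the significance level, sidedness and degrees of freedom beside the table so that the figures can be reproduced.

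If Table 3 stands:
- Restate the text as 13.0, 7.8 and 7.8 points (25, 18 and 29% reductions).
- Give effect sizes for risk and protective factors as about .18 to .29, and settle whether Total Protection is .28 or .29.
- Make the comparison with the 20 to 40% range from those figures: cigarettes just below it, lifetime alcohol at 25%, and 30-day alcohol at 29% with a note that it is not an initiation outcome.

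If Appendix G supports the text instead, correct Table 3. Either way the cost is a check of the appendix and a change of wording or table entries; the design and the planned analyses are untouched.

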## **SCIENCE-BASED PREVENTION: TESTING COMMUNITIES THAT CARE PROTOCOL AND STATISTICAL ANALYSIS PLAN**

### **Experimental Design and Methods**

In 13 of the 20 matched pairs of communities participating in the Diffusion project, neither community has progressed in the use of prevention science to the point of using tested effective policies and programs to address risk and protective factors elevated in epidemiologic community data. In the Diffusion project, these communities were matched within each state on population size, economic indicators, and crime data. Twelve pairs of these communities (24 communities) have been recruited to participate in the proposed study. One member of each pair has been randomly assigned to the CTC intervention condition; the other member of each pair has been assigned to the control group.

The intervention component will begin in the fall of Year 1, with a community activation and education process using Communities That Care training events, materials, and technical assistance. (See Appendix C for examples of the CTC community training guides from Developmental Research and Programs, the training and technical assistance subcontractor.) Intervention communities will be trained to use the baseline data collected in Year 5 of the Diffusion project, just prior to the start of the proposed study, to prioritize specific areas and risk and protective factors for attention. By the ninth month of the project, communities will select effective interventions to address their prioritized needs and create strategic community prevention plans to implement these interventions. Selected policies and programs will be offered to affect participants in the panel sample in each community beginning in the Fall of Year 2 and continuing through Year 5 of the study.

Effects of the CTC intervention on risk factors, protective factors, substance use, and other problem behaviors will be assessed using repeated cross-sectional and longitudinal student surveys in both intervention and control communities. Implementation and impact of the CTC intervention on communities' prevention service systems will be assessed using the CKI telephone interviews of community key informants, and the CRD surveys of prevention service providers in all communities.

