**Strengths of the proposed study design.** Conducting the proposed research with 12 pairs of communities participating in the Diffusion project provides several distinct advantages. These include: 1) three waves of baseline data measuring trends in risk, protection, and adolescent substance use, delinquency, violence, and related problems from student surveys conducted in each community prior to the start of the proposed study; 2) two waves of baseline data on each community's prevention planning approach including the degree of implementation of risk- and protective-focused prevention collected prior to the start of the proposed study; 3) two waves of baseline data on the number, types, and scope of science-based prevention strategies within each community collected prior to the start of the proposed study; and 4) a five-year history of collaboration between these communities and the researchers. Another strength of the proposed design is the combination of repeated cross-sectional surveys of students in four different grade levels with a longitudinal panel of students followed and surveyed annually for the five years of the project. Using the two survey methods, which provide complementary approaches to assessing intervention impact on risk, protection, and substance use and related problem behaviors, addresses different threats to the internal validity of study findings (Salonen et al., 1986; Wagner et al., 1991). Finally, the two assessment methods focus primarily on the age group

affected most directly by the prevention strategies implemented as a result of the CTC intervention, but also allow evaluation of the impact of broader community policy and norm changes on the prevalence of problem behaviors among older youths.

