The analysis will then assess the effects of intervention on changes over time in communities' levels of risk and protective factors. These analyses will use growth curve models (Bryk & Raudenbush, 1987; Diggle et al., 1995) at the community level to examine the effect of intervention on slopes of risk and protection over time. These are flexible models that allow the use of individual covariates and community-level time-varying covariates. Standard multilevel models will be used, with four levels of nesting: children at level one nested within survey occasion at level two, nested within communities at level 3, and nested within pairs at level 4. In this model, growth curves exist at level 2, in which the community average scores at each time point are modeled as a function of an intercept and slope that represents change over time. Again, treatment is a fixed community-level effect that predicts the slope of the growth curve at level 3.

In the analyses above, intervention condition is used as a predictor of differences and changes in risk and protective factors. We will also assess the effect of the intervention by examining the relationship between community implementation of the CTC strategy and risk, protection, and adolescent behavior outcomes. As described earlier, the CKI interviews conducted in the second and fourth year of the study will provide data to create implementation scores for each community. These are ratings of the extent to which each community has advanced in implementing the CTC strategy on a scale of 1 to 5. Using implementation scores in analyses will allow assessment of whether variation in the degree to which the CTC intervention was implemented is related to differential outcomes. These analyses follow those above and will use the implementation score as an independent variable at the community level.

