**Aim 2.** To examine effects of CTC on levels of collaboration across agencies, groups and organizations in communities.

**Aim 3.** To examine effects of CTC on community use of epidemiologic data to guide prevention service system planning.

Aims two and three address the effects of the CTC intervention on community-level outcomes. Community outcome analyses will be conducted using single level models since the outcomes are viewed as characteristics of the community. Since the analyses for both aims are the same, they are described together. Both cross sectional and longitudinal analyses will be conducted to assess average differences and changes in collaboration or use of epidemiological data over time as they relate to the intervention.

Differences between treatment and control communities in community-level outcomes will be assessed using standard General Linear Models (GLMs). Community covariates will be used to reduce the error

variance of each model and help explain reasons for differences between communities. Further longitudinal analyses using growth curves will assess the effects of intervention on changes in collaboration and use of epidemiologic data for strategic prevention planning over time. These growth curves can be assessed using either multilevel GLM techniques or structural equation models. The advantage of using structural models is that they allow more efficient modeling of ordinal variables providing more accurate estimates of parameters and standard errors (Muthén et al., 1997). These analyses will also utilize the information available for these communities for the five years prior to intervention. One method, as described above, for looking at student outcomes, is to use the slopes and intercepts from the baseline period as predictors of the slopes during the intervention period. This allows for assessing whether the intervention is able to change trajectories across time.

As in the first aim, comparisons of treatment and control communities will be elaborated by separate analyses testing the extent to which CTC implementation relates to these community-level outcomes.

**Aim 4.** To assess the degree to which the use of tested effective programs in communities predicts changes in community-wide levels and trajectories of risk, protection, and drug use and related health and behavior outcomes.

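### The Power section sizes a between-arm test of the implementation score above three, but no planned analysis uses that score as an outcome, and the cut at three is a weak form of the test

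*Protocol*

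**What the plan says.** The Power section, after the student outcomes, turns to communities. It describes power to "detect changes in implementation scores from three or less to above three was conducted using non-parametric techniques" and concludes that there is "adequate power to detect a significant difference if six more experimental communities than controls achieve the desired implementation result". It does not state the test, alpha, sidedness or the assumed control rate. Appendix G, to which the section refers for detail, is not part of the public text.

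The Analysis section gives the score a different role:

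- Aim 1 (cross-sectional cohort analyses): the models of risk, protection and behaviour "will use the implementation score as an independent variable at the community level".
- Aims 2 and 3: the arm comparisons, by general linear models and growth curves, are there to "assess average differences and changes in collaboration or use of epidemiological data over time as they relate to the intervention". Implementation then returns in "separate analyses testing the extent to which CTC implementation relates to these community-level outcomes".

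Elsewhere, Experimental Design and Methods says that "Implementation and impact of the CTC intervention on communities' prevention service systems will be assessed using the CKI telephone interviews" (with provider surveys alongside) but names no test. The Study Design section counts among its strengths two pre-trial waves on prevention planning, "including the degree of implementation of risk- and protective-focused prevention collected prior to the start of the proposed study".

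**The concern.** A power statement should belong to a test in the plan. Here the Power section treats the score as an outcome of randomisation, while the Analysis section treats it only as an explanatory variable. Relating observed implementation to youth outcomes is not a randomised comparison, and it does not show whether assignment to CTC raised the score.

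The second issue is the form of the comparison. With 24 communities and a rating from 1 to 5, reducing each community to above or not above three throws away most of the gradation, although the full score and a pre-trial value are available. At stake is a direct test of whether CTC moved communities on the measure designed to capture its implementation.

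**Working it through.** **1. Does the plan's figure reproduce as a between-arm test?** Inputs: "Since the community is the level of random assignment, the sample size is 24", split 12 and 12 within matched pairs. Assumed, because not stated: alpha 0.05, two-sided.

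- Fisher's exact test, 6/12 against 0/12: p = 2 × C(12,6)/C(24,6) = 2 × 924/134,596 = 0.014.
- With no control community above three, 5 against 0 is already significant (p = 0.037) and 4 against 0 is not (p = 0.093). At true rates 0.50 and 0, power = P(X ≥ 5), X ~ Bin(12, 0.5), = 1 − 794/4,096 = 0.806.
- A difference of six is significant at every control count from 0 to 6 (p from 0.014 to 0.039).

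So the statement reproduces, and only as a two-arm test with the score as outcome. It depends on the control rate: with 1/12 to 3/12 of controls above three, Fisher power for six more communities is 0.61 to 0.65. The exact McNemar test on the pairs needs 6 against 0, so its power at control rate 0 is 1 − 1,586/4,096 = 0.613.

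**2. Is that test anywhere in the analyses?**

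| Place in the protocol | Role of the implementation score |
|---|---|
| Power | Outcome, compared by arm, cut at three, non-parametric |
| Study Design, key informant samples | Not among the arm comparisons (collaboration, data use, choice of tested strategies) |
| Community Key Informant Interviews, Instrument | Stage of implementation is a construct separate from collaboration and data use |
| Avoiding cross-community contamination | Implementation measured in both arms, to identify contamination |
| Analysis, Aim 1 | Predictor |
| Analysis, Aims 2 and 3 | Predictor; the arm comparisons concern collaboration and data use |

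Because the score is a separate construct, the tests under Aims 2 and 3 do not cover it by implication.

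**3. What does the cut cost?** Assumptions: 12 pairs; normal scores held within 1 to 5; SD 0.9 (between the all-respondent values 0.79 and 0.97 in Table 2); Year 4 control mean 1.5; no within-pair correlation; two-sided alpha 0.05. The chance of scoring above three is 1 − Φ((3 − mean)/0.9), which is 0.048 for controls. Power for the cut is by exact enumeration; power for the paired t-test on the score is by simulation.

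| Intervention mean | P(above three) | Paired t, full score | Fisher, cut | Exact McNemar, cut |
|---|---|---|---|---|
| 2.5 | 0.289 | 0.68 | 0.15 | 0.06 |
| 2.75 | 0.391 | 0.86 | 0.35 | 0.21 |
| 3.0 | 0.500 | 0.96 | 0.60 | 0.45 |
| 3.25 | 0.609 | 0.99 | 0.81 | 0.71 |
| 3.5 | 0.711 | >0.99 | 0.93 | 0.88 |

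One caution on scale: an all-respondent mean of 1.08 with SD 0.79 cannot arise from 12 community scores with a floor of 1 if they are whole numbers (eleven 1s and one 2 give SD 0.29). Repeating the calculation on a 0 to 5 scale left the results essentially unchanged: 69/15/6% at 2.5, 88/35/21% at 2.75 and 96/60/46% at 3.0.

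**4. Illustrative detectable difference for the full score.** SD of a pair difference = 0.9 × √2 = 1.27; standard error = 1.27/√12 = 0.367; with 11 degrees of freedom, (2.201 + 0.876) × 0.367 = 1.13 points at 80% power, before any gain from baseline adjustment or matching.

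**The case against.** The Power section itself names the outcome, the unit, the contrast and the class of method, and the design section says that implementation will be assessed. The fair reading is that the comparison is intended and was not carried into an aim. That stands: alone, the omission would be a missing cross-reference, and the stated power figure is sound on its own terms.

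A reader might infer that CTC's effect on implementation is never tested, or that a null youth result could not be separated into failure to implement and failure to work. The documents support neither. Collaboration and data use are compared by arm. The number, scope, dosage and exposure of tested programs are documented in both arms. Board surveys, activity reports and fidelity measures are collected in the intervention communities. A between-arm test of the score would add to this evidence; without it there is still evidence.

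On the cut, crossing three is described as the desired result, so it is a stage target and not an arbitrary split. If CTC carries the average community well past three, little power is lost, as the last row of the table shows. That also stands, and is why the whole range is given. It does not make the cut the better primary comparison: in none of the scenarios does it have more power than the full score.

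**Conclusion.** The Power and Analysis sections do not match on the implementation score: it is powered as a between-arm outcome and analysed only as a predictor. The finding is limited to that score. It leaves the Aim 1 youth outcomes and Table 3 untouched.

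The loss from the cut is large if the intervention mean is at or below three (at 3.0, 96% against 60% or 45%) and small if it is well above (at 3.5, over 99% against 93% or 88%). These percentages rest on the assumed SD, Year 4 control mean and zero within-pair correlation, none of which the protocol gives for Year 4. The mismatch itself rests on the text alone.

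**What to change.** In Analysis, Aims 2 and 3, add the implementation score as a community-level outcome compared between arms: the Year 4 score on its full scale (and Year 2 likewise), within the 12 pairs, adjusted for the score from the Diffusion project. If normality is doubtful, a permutation test that swaps arms within pairs serves; the protocol already contemplates permutation tests for Aim 1.

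In Power, give the detectable difference for that test, with its alpha, sidedness, SD and assumed correlations. Keep the number of communities above three as a secondary, descriptive stage target.

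The cost is one extra model on data already to be collected and one recalculated power line.
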